### Objectives

This study will define the pathways that patients with suspected HPB malignancies take from presentation to the completion of treatment, in terms of times between key diagnostic tests, multidisciplinary team (MDT) meetings, management of jaundice, treatments, and outcomes. Furthermore, it aims to define the variation in these practices and the potential effect of this variation in observed outcomes. The intention of therapy for patients with an HPB malignancy is determined by whether the primary lesion is deemed surgically resectable or not. The secondary objectives of the study are sectioned by intent of therapy (ie, resectable or nonresectable). The details of the primary and secondary objectives can be found in Table 1. Audit standards of the RICOCHET study are shown in Table 2. While patients will be analyzed by resectional status, outcomes from palliative management, which may occur concurrently, will also be collected. Therefore, referrals to a palliative care team, rates of palliative chemotherapy, and reviews by a clinical nurse specialist (CNS) have been included in our data collection.

In undertaking a cross-specialty national study, we aim to develop a lasting collaborative research network that will provide a framework for future clinical research.

**Table 1 table1:** Primary and secondary objectives of the RICOCHET^a^ study.

Objectives and outcomes				Outcome measures
**Primary objective: To describe the management pathways and 90-day outcomes for patients who are investigated with suspected resectable and nonresectable cancer of the pancreas, periampullary tissues, and the major bile ducts**				

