	**Intention domains**			
		Curative surgery		Time from presentation to surgery Rates of completion of surgery with curative intent or awaiting surgery Histological staging Rates of adverse events
		Palliative and end-of-life care planning		Rates of referral to hospital or community palliative care team if appropriate Number of patients seen by a CNS^l^ Number of patients where ceiling of care and resuscitation status has been discussed
		Other outcomes		Number of inpatient days Number of unplanned admissions Death: time and cause

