**Patient survival after biliary decompression in palliative disease**		
	7 days [19,20]	>90
	30 days [21]	>75
Ability to proceed to palliative chemotherapy in patients with unresectable malignancy [22]		25

^a^RICOCHET: Receipt of Curative Resection or Palliative Care for Hepatopancreaticobiliary Tumours.

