### Case Identification, Inclusion, and Follow-Up

Aspects of health care in the United Kingdom are modelled on a hub-and-spoke design, which arranges service delivery assets into a network consisting of a tertiary care provider, the hub, complemented by secondary care providers, the spokes. The hub offers a specialist service, including resection, whereas the spokes offer a more limited service, routing patients needing specialist treatment to the hub [23].

Adult patients with a newly suspected HPB malignancy will be identified and screened for inclusion at participating sites over a 90-day, case-identification period. A patient will be included according to one of the three inclusion criteria: (1) suspected malignant pancreatic lesion, (2) suspected periampullary lesion, or (3) suspected malignant biliary obstruction caused by a primary malignancy of the liver hilum or extrahepatic biliary tree (see Figure 1). Exclusion criteria include the following: less than 16 years of age, recurrent HPB malignancy, suspected secondary malignancy (ie, metastatic disease of an origin outside of the HPB anatomical area), and gallbladder or intrahepatic lesions. Cases will be identified at four nodes: MDT meetings, CNS referrals, from biliary decompression lists, and any remaining modes of referral, including through outpatient clinic and ward referrals (see Figure 2). Upon inclusion to the study, each patient’s management and investigative pathways will be charted from their initial relevant presentation to hospital care at the participating site. This *day zero* will be defined as the chronologically primary relevant attendance to the emergency department, outpatient clinic, discussion of the case at MDT where a diagnosis of malignancy was first considered, or the date of the radiological or endoscopic imaging that identifies an incidental finding of malignancy. Cases will be mapped by the outcome measures described in Table 1 for 90 days from *day zero*. For cases in which a patient’s care is moved between a spoke and hub center, data will be collected from site-specific *day zero* for the following 90 days. For the purpose of analysis, we will primarily assess 90-day outcomes from the first *day zero*. However, we may explore extended time points as part of an exploratory outcome analysis. The differences in treatment and outcomes of patients across centers (ie, hub or spoke) will be analyzed.

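### With the primary analysis closed 90 days after first presentation, events after surgery are seen for only 90 days minus the wait, so the hub/spoke and decompression comparisons are distorted whenever waits differ

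*Protocol article*

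**What the plan says.** Under Case Identification, Inclusion, and Follow-Up, the Protocol article states: "Cases will be mapped by the outcome measures described in Table 1 for 90 days from" day zero. Day zero "will be defined as the chronologically primary relevant attendance to the emergency department, outpatient clinic, discussion of the case at MDT", or the date of imaging that gave an incidental finding. It is a presentation date, never a procedure date.

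The same section gives transferred patients a longer collection period: "For cases in which a patient’s care is moved between a spoke and hub center, data will be collected from site-specific" day zero for a further 90 days. The analysis nevertheless returns to the first clock: "For the purpose of analysis, we will primarily assess 90-day outcomes from the first" day zero. Later looks are optional: "However, we may explore extended time points as part of an exploratory outcome analysis".

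Table 1 (Intention domains, Curative surgery) places these measures under that clock: "Time from presentation to surgery Rates of completion of surgery with curative intent or awaiting surgery", followed by histological staging and adverse-event rates. No period after surgery is attached to the adverse events. The secondary objectives for resectable disease compare these measures between jaundiced patients with and without preoperative decompression, and between patients who first attend a hub and those who first attend a spoke.

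Table 2 is different. Its standard on "Patient survival after biliary decompression in palliative disease" is set at 7 and 30 days, counted from the procedure.

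**The concern.** A window that starts at presentation suits a description of what has happened to patients by day 90. It does not suit outcomes that can only begin at a later procedure. For those, observation time depends on how quickly the pathway delivered the procedure, and pathway speed is one of the things the study compares.

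Two groups with identical surgical safety would then show different complication rates if one waits longer, and the slower one would look safer. Likewise, any summary of waits that uses only patients already operated on would shorten the slower group's wait more. The Discussion says the study is meant to find bottlenecks, and both distortions work against that aim.

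**Working it through.** **From the document alone.** Post-operative observation = 90 − W, where W is days from first day zero to surgery.

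- W = 20: 90 − 20 = 70 days.
- W = 75: 90 − 75 = 15 days.
- A full 30 days after surgery requires W ≤ 60.

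The direction of the distortion follows from this and needs no assumption about the distribution of waits.

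**Follow-up beyond day 90.** A transferred patient has data for 90 days from the second site's day zero. If that falls on day 25 (an assumed figure), collection runs to 25 + 90 = day 115. A patient who stays at one site has data to day 90 only. Because resection is done at hubs, the extra time goes to patients who start at a spoke. Extended analyses would therefore also have uneven follow-up, by transfer status.

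**Illustration of size.** The article gives no waiting times or complication rates, so all inputs here are assumed:

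- W is log-normal with median m = 50 or 80 days and log-SD s = 0.3, 0.5 or 0.7.
- The true post-operative event rate is 30%, with exponential onset, mean 15 days.

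Formulas, with Φ the standard normal distribution function:

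- Operated by day t: F(t) = Φ(ln(t/m)/s).
- Share of operated patients with under 30 days of follow-up: 1 − F(60)/F(90).
- Observed median among the operated: m·exp(s·Φ⁻¹(F(90)/2)).
- Observed event rate: the mean of 0.30·(1 − e^(−(90−W)/15)) over patients with W ≤ 90.

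Worked case, s = 0.5:

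- m = 50: F(90) = 0.880, F(60) = 0.642, so 1 − 0.642/0.880 = 27%.
- m = 80: F(90) = 0.593, F(60) = 0.283, so 1 − 0.283/0.593 = 52%.

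| s | Operated by day 90 (m = 50 / 80) | Observed median wait, days | Under 30 days of follow-up | Observed event rate (true 30%) |
|---|---|---|---|---|
| 0.3 | 98% / 65% | 50 / 70 | 25% / 74% | 26% / 20% |
| 0.5 | 88% / 59% | 46 / 61 | 27% / 52% | 26% / 23% |
| 0.7 | 80% / 57% | 42 / 54 | 25% / 40% | 26% / 24% |

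Equal true risks appear 2 to 6 percentage points apart. A true 30-day difference in median wait appears as about 20, 15 and 12 days if only operated patients are summarised.

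**Check of the remedy.** With a fixed 30-day window completed for each counted procedure, the rate is 0.30·(1 − e^(−30/15)) = 25.9% in both groups, whatever the wait.

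**The case against.** The strongest reply is that the primary objective is to describe pathways and 90-day outcomes, and a fixed window from presentation is a legitimate choice for that. The comparisons are secondary, the Discussion discloses the 90-day limit, and analytic methods may sit in a plan not shown. This stands for the descriptive aim, and overall deaths by day 90 from presentation are indeed followed equally in all groups. It does not settle the point, because the window and its origin are fixed here, and the same measures are carried into the comparisons. The stated limitation covers medium- and long-term outcomes; a complication 20 days after a day-75 operation is short-term and is still lost.

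A reader might infer several stronger things that the article does not support:

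- **That all outcomes stop at day 90.** Collection continues for transferred patients and extended time points are allowed. Only the primary analysis is closed at day 90.
- **That waiting patients are pooled with resected ones.** The Table 1 entry can equally mean two reported categories.
- **That waits will be summarised among operated patients only.** No section says so. The shortened medians above apply only if that were done.
- **That the slower group is flattered on surgery rates.** It looks worse: 88% versus 59% operated by day 90 at s = 0.5.
- **That the decompression survival standards are badly affected.** They already run from the procedure, and with an assumed 30-day survival of 73% the crude overstatement is only 0.1 to 1.2 points.

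The size also depends on when events occur. With median waits of 25 and 55 days (s = 0.5), a true 6% 90-day post-operative mortality appears as 4.1% versus 2.6% if deaths are spread evenly over 90 days, but 5.8% versus 5.1% if they come early (exponential, mean 15 days). Post-operative mortality at 90 days is not a listed outcome, so these figures show sensitivity only.

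**Conclusion.** The point holds for procedure-related outcomes in the primary analysis, chiefly adverse events after surgery. Their observation time is 90 days minus the wait, and time to surgery is cut off at day 90. If the compared groups differ in time to surgery, complications are under-counted more in the slower group.

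The direction is certain, but the size is not known. Under the assumed waits, equal true risks separate by about 2 to 6 percentage points, and 40–74% of operated patients in the slower group lack 30 days of post-operative follow-up, against 25–27% in the faster one. If waits do not differ between groups, rates are still understated but the comparison is not distorted by this route. Neither the stated limitation nor the optional later time points correct it.

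**What to change.** 1. Count procedure-related adverse events and deaths from the procedure over a fixed 30-day window. Either restrict to procedures done by day 60 of the first clock, or keep all procedures and use time-to-event methods with censoring at day 90.
2. Analyse time to surgery as cumulative incidence of resection by day 90 in all patients planned for resection. Censor those still waiting at day 90, and treat death or a decision against surgery as competing events.
3. Report patients resected by day 90 and patients awaiting surgery at day 90 as separate categories.

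This uses dates already collected and needs no new data. Restricting to day 60 drops late procedures (27% and 52% of operated patients in the s = 0.5 illustration) and describes earlier operations only. The time-to-event option keeps them at some loss of precision, and it assumes that, given the wait, censoring is unrelated to risk.

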**Figure 1 figure1:**
[figure not shown]
Schematic of the liver and pancreas showing the inclusion criteria for the study. To be included, patients must have one of the three indicated inclusion criteria.

**Figure 2 figure2:**
[figure not shown]
Case identification for the study. HPB: hepatopancreaticobiliary; REDCap: Research Electronic Data Capture.

### Sample Size

The RICOCHET study aims to involve all hub and spoke centers across the United Kingdom, and we expect to reach 75% of the cases during our inclusion period. Based on the follow-up period of 90 days and the annual incidence of the included HPB malignancies in the United Kingdom, we project the inclusion of approximately 1835 cases [1].

### Center Recruitment and Research Network

All centers that identify or refer HPB malignancies (N=227) are eligible to participate in this study (see Figure 3). The RICOCHET study will be open to all hub and spoke centers across the United Kingdom. Recruitment will take place via conferences, social media, established research contacts, trainee collaborative research networks, and from the use of the RICOCHET website [24].

**Figure 3 figure3:**
[figure not shown]
Schematic of the United Kingdom showing the location of all centers eligible for recruitment.

### Project Management

A steering committee—formed from doctors in training alongside one medical consultant and one surgical consultant—has designed, implemented, and overseen the study as well as the analysis and dissemination of results on completion. Regional collaborators will be organized as geographical regional leads (1-2 per region; 17 regions) that will support participating sites (up to 227 sites); they consist of local consultants (1-2 per site), local leads (1 per site), and data collection teams (1-5 collectors per site) (see Figure 4). It will be encouraged that both consultant surgeons and physicians work together as part of a multidisciplinary approach. The involvement of clinical nurse specialists, research nurses, and MDT coordinators will also be encouraged. Patient representatives are involved in every step of the development of this study.

**Figure 4 figure4:**
[figure not shown]
The Receipt of Curative Resection or Palliative Care for Hepatopancreaticobiliary Tumours (RICOCHET) research network.

### Data Collection

Case identification and follow-up will be undertaken in the same manner at all sites. The local data collectors are either medically trained, ranging from medical students to consultants, or specialist nurses in HPB surgery or oncology. Site- and case-specific data will be entered onto Research Electronic Data Capture (REDCap), an established Web application that allows collaborators to enter and store data [25]. The REDCap server for the RICOCHET study is hosted by the Birmingham Surgical Trials Consortium, University of Birmingham, Birmingham, UK, under license from Vanderbilt University, Nashville, Tennessee. REDCap allows electronic data collection and can be accessed via a Web browser or an app on a tablet or mobile phone. REDCap has been used successfully in over 120 different countries and in more than 500,000 projects around the world [26-28].

### Data Linkage Across Sites and Pseudonymization

The RICOCHET study will involve a large number of sites across the United Kingdom to include both hub and spoke centers. Patient care may be transferred from spoke centers to specialist hub centers for discussion and/or treatment. In order to record a patient’s complete pathway, data will be collected from all sites involved in a patient’s care. However, the centers involved in the RICOCHET study have isolated, independent computer and data storage systems, with no means of centralized data access. To overcome this problem, the study will utilize a system of pseudonymization that assigns a case identifier to a patient’s REDCap records, which can be used to link REDCap data.

Data collection teams at each site will be sent the OpenPseudonymiser program via individual USB sticks. OpenPseudonymiser is a free, open-source, standalone Windows application [29] that uses the principles outlined by the Information Commissioner’s Office on data protection [30]. It has been designed to comply with national information governance requirements for the transfer of unidentifiable confidential data. OpenPseudonymiser checks the validity of the National Health Service (NHS) number within a comma-separated variables file, attaches extra encrypted data to the NHS number, then encrypts the combination using the international standard Secure Hash Algorithm 256 (SHA-256) to produce a string of output characters, known as the digest. The digest can then be used as the case identifier within REDCap. It enables data linkage across sites, as using the same NHS number with the same encryption will produce the same digest. Therefore, pseudonymization of the NHS number for each case can be achieved before being uploaded onto REDCap to maintain confidentiality of patient data and allow data linkage across sites.

A successful pilot study was carried out by the RICOCHET committee and involved testing of the REDCap and pseudonymization systems to allow accurate patient data linkage across hub and spoke sites before being rolled out nationally.

### Statistical Analysis

Upon data collection and dissemination, data distribution will be determined and appropriately summarized. Frequencies and percentages will be used for categorical variables. Univariate and multivariate analyses will be assessed by appropriate statistical techniques. A *P* value of less than .05 will be considered significant for statistical methods used. The analysis will be completed by suitable statistical software.

### Ethics, Consent to Participate, and Dissemination

The RICOCHET study is a prospective study mapping patient investigative and management pathways. An intervention involving the patient’s health care will not be implemented; therefore, patient consent is not required for the RICOCHET study. This has been confirmed using the national UK decision-making tool of the NHS Health Research Authority and the Medical Research Council [31]. The RICOCHET study will therefore be locally registered as a clinical audit or service evaluation project at all participating sites prior to patient identification and data collection.

### Availability of Data and Material

The datasets used and/or analyzed during the current study are available from the corresponding author upon reasonable request.

## Results

The RICOCHET study results and analyses will be subject to peer review by presenting them at international cross-specialty conferences and by submitting them for publication in open-access journals. Moreover, our findings will be presented to patient groups and sponsoring charities (eg, Pancreatic Cancer UK), who in turn will disseminate key findings to the primary beneficiaries of the results: the patients. The RICOCHET study was funded in September 2017. Data collection started in April 2018 and the planned end date for data upload is spring 2019. Data analysis will take place in the summer of 2019 and the first results are expected to be published in late 2019 or early 2020.

## Discussion

Survival among patients with pancreatic cancer has not improved over the past 40 years, a fact that demands the attention of health care providers, users, and service designers [32,33]. Nevertheless, there are grounds for optimism. Adjuvant chemotherapy is increasingly effective, correction of pancreatic exocrine insufficiency can improve survival, and optimized diagnostic pathways can reduce the time to surgery and improve resection rates [9,34,35]. These are just a few examples of where progress is being made. Optimizing pathways, reducing variation in practice, and national guidance can all help achieve improvement. While more substantial improvements may occur from novel chemotherapeutics, it is clear that outcomes and patient experience can be improved by focusing on optimizing every part of the patient pathway, from diagnosis to treatment [36]. It is therefore essential that current practice and its variation and effect on patient outcomes are evaluated. This study closely follows the publication of the first NICE guidelines for the management of pancreatic cancer in the United Kingdom [16]. Real-world practice may stray from guidelines for a multitude of reasons, including limitations of local resources and expertise, case-specific vagaries, and, in some cases, perceived equipoise in the available data [9]. There may also be a tendency to overinvestigate patients, with consequent delays to treatment [10]. The RICOCHET study aims to reveal the main bottlenecks in the pathways and identify where improvements can be made.

The 15% of patients with potentially resectable disease are frequently the focus of clinical research, with a limited emphasis on the considerably larger proportion of patients with nonresectable disease [37]. The RICOCHET study is a comprehensive study of practice among all patients with suspected cancer, regardless of stage or treatment options. Analysis of Hospital Episode Statistics data demonstrates a remarkably high 30-day mortality rate among patients with malignant biliary obstruction, but the cause for this high incidence remains unknown [19]. A further benefit of the RICOCHET study is, therefore, to target areas where there is a particular need for more in-depth information.

Collecting patient-level data across hospitals with linkage presents significant ethical challenges. The use of the OpenPseudonymiser tool to link patient data across independent sites overcomes this potential prohibitive barrier to patient-pathway mapping. Successful implementation of this system in an ambitious nationwide study will provide a blueprint for future collaborative research that requires linking patient data from discrete sites.

The RICOCHET study has several limitations. The study has been designed to assess patient pathways against contemporary guidelines [16,17]. The 90-day patient follow-up period reflects this, but denies the assessment of medium- and long-term outcomes. We expect that the data gathered by the RICOCHET study will inform focused cohort studies and randomized controlled trials that are designed to comprehensively answer questions about medium- and long-term outcomes. Furthermore, the nature of this observational study precludes an assessment of quality of life and patient-reported outcomes; these are critical in the meaningful assessment of care in patients with cancer, resectable or otherwise [38]. Over the course of the RICOCHET study, we aim to involve more than 500 collaborators across specialties, creating an extensive network of enthusiastic individuals. It will build a strong foundation for future collaborative research and strengthen interest in improving patient care in the NHS and beyond.

In conclusion, the RICOCHET study is an ambitious, multidisciplinary, multicenter, prospective observational study utilizing a novel design to achieve full coverage of the different patient pathways. It is led by trainees and builds on an extensive national collaborative network. The study aims to highlight the variation in practice and its effect on the outcomes of patients with HPB malignancies. It may then provide evidence to develop a more standardized approach to managing patients with suspected HPB malignancy.

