	**Management pathway domains**			
		Presentation to secondary care		Presentation to outpatient clinic, emergency admission, referral from spoke center, incidental radiological finding, etc
		Principal care point		Whether first presentation was at a hub or spoke center^b^
		Utility of MDT^c^		Whether case discussed at MDT meeting Timing with reference to presentation and frequency

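### Patients of non-participating spokes enter only through a participating hub, so capture depends on the pathway under study and probably, though not certainly, under-represents locally managed nonresectable patients

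*Protocol article*

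**What the plan says.** All points are from the protocol article.

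- **Where cases are found** (Case Identification, Inclusion, and Follow-Up): "Adult patients with a newly suspected HPB malignancy will be identified and screened for inclusion at participating sites over a 90-day, case-identification period".
- **Who joins** (Center Recruitment and Research Network): all 227 centers are eligible, and "Recruitment will take place via conferences, social media, established research contacts, trainee collaborative research networks". Project Management gives 227 as the upper limit on sites.
- **Expected coverage** (Sample Size): "we expect to reach 75% of the cases during our inclusion period", with about 1835 cases projected. The 75% is not split by hub and spoke.
- **Who moves to a hub**: hubs offer resection, "whereas the spokes offer a more limited service, routing patients needing specialist treatment to the hub" (Case Identification). Data Linkage Across Sites and Pseudonymization adds: "Patient care may be transferred from spoke centers to specialist hub centers for discussion and/or treatment".
- **What is recorded**: Table 1 collects mode of presentation, with "referral from spoke center" as one category, and whether first presentation was at a hub or a spoke. The pseudonymized digest links records across sites.
- **How the cohort is described**: "The RICOCHET study is a comprehensive study of practice among all patients with suspected cancer, regardless of stage or treatment options" (Discussion). The abstract's conclusions and the closing paragraph of the Discussion also speak of full coverage of pathways.
- **Limitations** (Discussion): short follow-up and the absence of quality-of-life and patient-reported data. Selective capture is not listed.

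**The concern.** The quarter of cases expected to be missed need not resemble the rest. A spoke patient who is passed on has two chances of capture, at the spoke and at the hub. One who is managed locally throughout has only the first. If the spoke does not take part, the referred patient can still be picked up and the locally managed one cannot. Entry then depends on referral, which is part of the pathway the study sets out to describe.

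The primary objective is to describe pathways and 90-day outcomes in both resectable and nonresectable disease. The Discussion argues that the nonresectable majority gets too little research attention, and this is the group most exposed to under-capture. A larger sample would not remove such a bias. Selection could also act within the nonresectable group, and so touch the palliative rates and the Table 2 audit figures, if those who reach a hub differ from those who do not.

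**Working it through.** **1. The plan's own figure.** Projected N should equal annual incidence × (90/365) × 0.75. The incidence is cited but not printed, so 1835 can only be inverted: 1835 / (0.75 × 90/365) = about 9,923 cases a year. If the 75% is already inside the 1835, the window holds 1835 / 0.75 = about 2,447 cases, of which about 612 are missed. Nothing in the article says where those cases arise.

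**2. Bound on the resectable share.** Inputs: true share r = 0.15 (a background figure in the Discussion, taken here as true) and overall coverage 0.75 (Sample Size). Let cR and cN be the capture probabilities of resectable and nonresectable cases.

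- Constraint: 0.15·cR + 0.85·cN = 0.75
- Observed share = 0.15·cR / 0.75

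| cR | cN | Observed share | Of 1835 |
|---|---|---|---|
| 50% | 79.4% | 10.0% | 183 |
| 75% | 75.0% | 15.0% | 275 |
| 85% | 73.2% | 17.0% | 312 |
| 90% | 72.4% | 18.0% | 330 |
| 100% | 70.6% | 20.0% | 367 |

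The ceiling is 5 points above the true value, or one third in relative terms. The sampling half-width is 1.96 × √(0.15 × 0.85 / 1835) = 1.6 points.

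**3. Two chances of capture.** Let q be the fraction presenting first at spokes, ps and ph the capture probabilities at spokes and hubs, and h the fraction of nonresectable spoke cases that reach a hub. All resectable cases are taken as referred. All four values are assumptions.

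- Resectable captured: R = 0.15 × [(1−q)·ph + q·(ps + (1−ps)·ph)]
- Nonresectable captured: N = 0.85 × [(1−q)·ph + q·(ps + (1−ps)·h·ph)]
- Observed share = R / (R + N)

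With q = 0.8, ps = 0.70, ph = 1 and h = 0: R = 0.150 and N = 0.646, so the share is 0.150 / 0.796 = 18.8%. For h = 25%, 50%, 90% and 100% it is 17.7%, 16.7%, 15.3% and 15.0%. With ps = ph = 0.75 it is 17.5% at h = 0 and 16.1% at h = 50%. Coverage in these runs is above 75% (77% to 100%), so they show direction and rough size and are not calibrated to the plan.

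**4. Can the direction reverse?** Yes. Take q = 0.8, ps = 0.8, ph = 0.5, h = 0.5 and hub-first patients 30% resectable, so that spoke-first patients are (0.15 − 0.2 × 0.30) / 0.8 = 11.25% resectable.

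- R = 0.2 × 0.30 × 0.5 + 0.8 × 0.1125 × 0.90 = 0.111
- N = 0.2 × 0.70 × 0.5 + 0.8 × 0.8875 × 0.85 = 0.6735
- Share = 0.111 / 0.7845 = 14.1%

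Low hub participation alone is not enough in this model. With hub-first patients also 15% resectable, the share is 15.7%.

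**5. Does the surgery rate follow?** Not necessarily. Suppose every resectable patient is operated on, but the operation is recorded only at a participating hub. With ps = ph = 0.75 the numerator is 0.15 × 0.75 = 0.1125. The observed rate is 0.1125 / 0.7725 = 14.6% at h = 0 and 0.1125 / 0.8363 = 13.5% at h = 50%, below the true 15%, although the resectable share in the same runs is above 15%.

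**6. Mortality.** At 75% coverage the error is 0.25 × (mortality in missed minus captured cases). The article gives neither term, so no size follows.

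**The case against.** - **The scope sentence can be read as eligibility.** In context it contrasts a study open to any stage with research confined to resectable disease. The full-coverage wording refers to pathways, and the 75% openly concedes incomplete capture. This reading is fair, so the sentence is not a plain contradiction of the Sample Size section. What stands is that the article nowhere says the missed cases may differ.
- **Nonresectable patients also reach hubs.** Transfer may be for discussion only, MDT meetings are an identification node, and neither decompression lists nor specialist nurse referrals are specific to resectable disease. This shrinks the bias. It removes it only if nonresectable cases reach participating hubs as often as resectable ones, which the article does not say. MDT discussion is itself a recorded outcome in Table 1.
- **A reader might infer that the resectable share and surgery rate are definitely too high, and palliative-only care and early death too low.** The document does not support that: steps 4 and 5 show that the share can reverse and that the surgery rate can move the other way.
- **No pooled resectable share is planned.** Table 1 does not list it, and analysis is to be by resectional status. A changed mix between the two groups does not by itself bias results within each. This limits what step 2 shows. Selection within the nonresectable group remains possible but cannot be quantified.
- **Denominators belong in a fuller plan that is not shown.** That is true of the detail. The coverage wording and the limitations list are in the article and can be judged as they stand.

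**Conclusion.** The concern holds as an unacknowledged risk of selective capture. Among spoke-first patients, the article's own rules give referred patients more chances of entry than locally managed ones. Under-representation of locally managed nonresectable patients is therefore the likely direction, but it is not certain.

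The observed resectable share would be 15% under equal capture and at most 20%. The ceiling requires capture of every resectable case. The share could fall below 15% if hubs take part less than spokes and hub-first patients are more often resectable. These figures rest on 15% being the true share in this cohort and on 75% coverage being achieved; every participation and referral value in steps 3 to 5 is assumed. No size can be given for surgery, palliative care or mortality rates. The point merits a change to reporting and wording. It does not show that any planned estimate is wrong.

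**What to change.** 1. For rates presented as national (surgery, palliative care referral, palliative chemotherapy, 90-day outcomes), report beside the full cohort an analysis restricted to patients whose first presentation was at a participating center.
2. Describe separately the hub records marked "referral from spoke center" that have no linked spoke record. State that some may be linkage failures or cases missed by a participating spoke. For that reason the restricted analysis should accompany the full cohort and not replace it.
3. Report participation out of the 227 eligible centers, by hub/spoke and region.
4. Add selective capture to the limitations in the Discussion.
5. Qualify the wording about all patients (Discussion) and about full coverage (abstract conclusions and closing paragraph) by the coverage achieved.

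The cost is small: mode of presentation, hub or spoke first presentation and the linkage digest are already collected. The downside is a smaller denominator in the restricted analysis. That analysis removes capture that depends on referral. It does not make voluntary participation representative, and it does not recover operations at non-participating hubs.
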